### Recruitment

Potentially eligible participants in Alberta are identified through media outreach, promotional pamphlets, community based networks, and by cancer registry case records to mail study invitation letters. In Alberta, only one major cancer centre has MBSR classes specifically for individuals diagnosed with cancer; therefore all individuals who are unable to attend these F2F classes would be eligible to participate. The Alberta Cancer Registry estimates as of September 2011, 25,000 individuals diagnosed with cancer are eligible to be contacted for the trial. According to research conducted by the PI, approximately 35-45% of these individuals will meet criteria of being distressed. Additionally, 77% of Albertans 16 years of age and older have Internet access and 429 communities throughout the province of Alberta have broadband Internet (http://www.albertacanada.com; http://www.albertasupernet.ca). This forms a potentially large cohort to identify individuals living with cancer who have Internet access for this study.

### Procedures

The study, including its nature, outcomes, and extent of participant involvement, is discussed with all prospective participants. Consent is obtained, and participants are informed that they can refuse to answer any question and they can withdraw from the study at any time. On average the quantitative assessments take 30–45 minutes. Before and after the 8-week online MBSR intervention, participants complete an identical battery of questionnaires (T1 & T2). These assessments are completed online in a secure environment with reminder follow-up emails/phone calls placed to participants who fail to complete their questionnaires within two weeks of expected receipt. Two follow-up email reminders separated one week apart are sent and, if no response, a maximum of three attempts to remind patients via telephone at different times of the day are made, with messages left. Participants who are randomized to the control group complete an additional assessment (T3) following their participation in the MBSR program after waiting.

### Screening, consent and enrollment

At first contact, interested participants are informed of the protocol and randomized design of the study. If interested, researchers ensure that individuals meet basic eligibility criteria. Potentially eligible participants complete the distress screen by phone conducted by the research coordinators. If interested and eligible, study procedures are explained in detail and consent obtained. Consent is also obtained to access medical records to confirm tumour location, stage and treatments received. Due to the lack of F2F contact during screening and consent, additional time is allocated to ensure fully informed consent by providing potential participants the opportunity to ask clarifying questions electronically or telephonically, and to require that the participant affirm that s/he has read the document, understands it, and has been presented with the opportunity to ask questions.

Researchers then provide a questionnaire package (including demographics and medical history, mood, stress, mindfulness, posttraumatic growth and spirituality measures) to complete online. Once a cohort is in place, participants are randomly allocated to one of two conditions using an online research randomization tool. All allocations are computer-based and not predictable. This process eliminates introduction of experimenter bias into participants’ group assignment. Once randomized participants are informed of group assignment (i.e., the immediate MBSR or the wait-list control condition) they are mailed a web-camera, headset, and MBSR course materials before they begin the program. Technical staff guide participants through installation of the equipment and online classroom tools in an orientation session before the first MBSR class. Those participants randomized to the wait-list condition are informed of their program start date and contacted closer to such date to send course materials.

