### Intervention group – online MBSR for cancer (Mindfulness-based Cancer Recovery – MBCR)

Components of the MBCR program include: didactic instruction, experiential practice, and group process. Didactically, specific topics covered within the 2 hour sessions and in the participant manual are: (a) concepts fundamental to mindful living and mindfulness meditation, (b) emotional, behavioural and cognitive patterns, and how such patterns can influence individual stress responses, and (c) the physical and psychological symptoms of stress and the influence of stress on physical and psychological health. Participants are instructed to apply principles taught didactically, through experiential practice of mindfulness meditation during group sessions and also as homework between formal classes. Guided meditation recordings and videos are distributed to support home practice. Participants are expected to practice 45 minutes of meditation and yoga postures daily. During class sessions the instructor guides participants through experiential activities including gentle Hatha yoga, qigong mindful movement, and various types of mindfulness meditation such as sitting and walking meditations. The instructor facilitates group discussions to encourage conversation around challenges experienced with meditation practice. Both fellow participants and the instructor offer support and feedback to assist in problem solving when difficulties are encountered during meditation practice. The instructor encourages communication and support between group members to enhance the group process [12].

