The online MBCR intervention was modeled after the F2F MBCR group intervention described above. The online format that most closely resembles F2F interaction (ability to see, hear and interact with group members in real time) is a synchronous online intervention with video and audio capabilities. In collaboration with the online education company eMindful Inc. (http://www.emindful.com), participants are able to access eMindful’s online virtual classroom and participate in real-time, online, synchronous, 2-hour MBCR classes for 8 consecutive weeks. Participants are asked to engage in the interactive features of the eMindful virtual classroom during the online classes. This includes logging on to the virtual classroom website, watching and listening in “real time” to streaming video and audio of the class instructor and other group participants on their computer screen, “chat” with the instructor and other group participants using a keyboard, and interactively participate using the headsets, web-cameras, and keyboards. Live images through the web-camera facilitate interaction with the instructor and other participants.

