### Treatment as Usual (TAU) wait-list control condition

In parallel with the online MBCR program, the TAU wait-list condition completes pre (T1) and post (T2) assessment measures before and after their wait period. Additionally, following the wait period, the control group completes the online MBCR intervention and completes one additional assessment time point (T3).

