### Analytic strategy

#### Analysis of power for primary effects

The target sample size for this study was based on achieving adequate power for the secondary analyses (since the primary analyses were proportions based on feasibility). The goal was to have 80% power at a significance level of .05, to test the efficacy of the online MBCR intervention in reducing mood disturbance, compared to the control group. On the basis of observed means and standard deviations in three F2F comparable trials [22,26,46]: the estimated effect sizes for group differences in pre- to post-intervention change on the POMS total mood disturbance score was 0.72, 0.51 and 0.58 respectively. Based on the three trials above, and following the more conservative estimation rule proposed by Dattalo (2008) [47] to use t-test estimations for RM-ANOVA designed studies, 26 participants are required for each group to detect a significant difference between the groups. Taking into account the likelihood of 20% attrition as observed in F2F MBSR trials, a total of 32 participants will be recruited for each group—a total sample size of 64 participants.

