### Secondary objective – primary outcome

Total Mood Disturbance scores will be examined with a 2 (group) × 2 (time) RM-ANOVA to examine main effects of time and group, and any interactions between time and group. Post-hoc analyses will be conducted to examine the simple main effects for treatment if a significant interaction is detected.

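### The efficacy model omits both the randomisation cohort, which costs precision, and the MBCR class, which understates the standard error if outcomes correlate within class

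*Protocol article*

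**What the plan says.** **Allocation.** Under Screening, consent and enrollment: "Once a cohort is in place, participants are randomly allocated to one of two conditions". The unit is the individual, and allocation happens cohort by cohort after baseline questionnaires are provided.

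**Delivery.** The Intervention group section has participants "participate in real-time, online, synchronous, 2-hour MBCR classes for 8 consecutive weeks". Group process is one of its three named components: "The instructor encourages communication and support between group members to enhance the group process".

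**Control.** Under the TAU wait-list section, controls complete T1 and T2 around their wait and take the programme only afterwards, with a further assessment at T3. No control has been in a class when T2 is measured.

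**Analysis.** Under Secondary objective – primary outcome, POMS Total Mood Disturbance is analysed by a two-by-two "RM-ANOVA to examine main effects of time and group" and their interaction. The next section applies the same strategy to stress, mindfulness, spirituality and posttraumatic growth. No cohort or class term appears.

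**Sample size.** Under Analysis of power for primary effects: "The goal was to have 80% power at a significance level of .05". The method is "to use t-test estimations for RM-ANOVA designed studies", giving 26 per group, raised to 32 per group for 20% attrition. There is no design effect.

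**The concern.** The stated model and sample size treat all participants as independent, while the article describes two kinds of grouping.

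- **Cohort** is shared by both arms. Participants enrolled together share a season and a calendar period, and may change alike between T1 and T2.
- **Class** exists before T2 in the MBCR arm only. Peers who support one another for eight weeks may move together. The T1-T2 comparison is then partially nested: one arm is clustered and the other is not.

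The two omissions act in opposite directions. Ignoring cohort tends to widen the standard error of the treatment contrast. Ignoring a positive class correlation narrows it, so p-values would be too small and the power figure too high. The efficacy claim on mood and the four other patient-reported outcomes is at stake. The primary feasibility objective rests on proportions and is not affected.

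**Working it through.** **The plan's own figure.** A two-sided t-test at 5% with 80% power needs 32 per group for the cited effect of 0.72, 62 for 0.51, 48 for 0.58 and 45 for their mean, 0.603. It does not return 26, which corresponds to an effect of about 0.79. That is a separate matter. Here 26 is taken as the number evaluable per arm (32 × 0.8 = 25.6).

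**Inputs.** From the article: 26 evaluable per arm, two-sided 5%, clustering before T2 in one arm. Assumed, because the article does not give them: two to four MBCR classes, so m = 13, 8.7 or 6.5 per class, and a class ICC of 0.02, 0.05 or 0.10. The relevant ICC is that of the T1-T2 change, since the group-by-time interaction in a two-by-two design is equivalent to a t-test on change.

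**(a) Cohort only.** Take four cohorts with 8 per arm in each (32 per arm), unit variance of change, and a share ρ of that variance due to cohort. With balance in each cohort, the cohort effect cancels from the contrast:

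- true SE = √(2(1−ρ)/32)
- expected SE from the unadjusted test ≈ √(2[(1−ρ) + ρ × 24/31]/32)

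At ρ = 0.05 these are 0.2437 and 0.2486 (2% too large). At ρ = 0.10 they are 0.2372 and 0.2472 (4% too large). Simulation with 40,000 replicates per scenario gave type I errors of 0.047 and 0.044, against 0.049 with no cohort or class effect.

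**(b) Class only.**

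- design effect in the MBCR arm: DE = 1 + (m−1) × ICC
- variance of the arm difference relative to independence: (1 + DE)/2, because only one arm is clustered
- true type I error = 2[1 − Φ(1.96/√((1+DE)/2))]

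Worked case, m = 13 and ICC 0.05: DE = 1.60; factor 1.30; SE ratio 1.140; 1.96/1.140 = 1.719; type I error 0.086.

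| Participants per class | ICC 0.02 | ICC 0.05 | ICC 0.10 |
|---|---|---|---|
| 6.5 (four classes) | 0.056 | 0.066 | 0.083 |
| 8.7 (three classes) | 0.059 | 0.073 | 0.096 |
| 13 (two classes) | 0.064 | 0.086 | 0.121 |

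The SE ratio runs from 1.027 to 1.265, so the reported SE would be 2.6% to 20.9% too small (1 − 1/ratio). At ICC zero there is no error.

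**(c) Both together.** Simulated with four cohorts and 8 per arm per cohort:

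| Class ICC | No cohort effect | Cohort ICC 0.05 | Cohort ICC 0.10 |
|---|---|---|---|
| 0.05 | 0.070 | 0.066 | 0.062 |
| 0.10 | 0.094 | 0.087 | not run |

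The cohort effect offsets part of the class effect, but not all of it in these scenarios.

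**(d) Power.** With the mean effect of 0.603, 26 per arm and m = 8, the normal approximation gives Φ(0.603 × √13 / r − 1.96), where r is the SE ratio. Power is 59% under independence (r = 1), 52% at ICC 0.05 (r = 1.084) and 47% at ICC 0.10 (r = 1.162).

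**The case against.** **Individual randomisation within cohorts might be read as a cause of a too-small SE.** It is not. A cohort effect common to both arms cancels from the contrast when the arms are balanced within cohort, and leaving it out errs on the conservative side. The article does not say whether allocation is balanced in each cohort. Without balance the unadjusted SE would be about right rather than too large, and precision would still be lost.

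**A reader might also infer that the SE is definitely too small.** The documents do not support that. It needs a positive class ICC in change scores, and no ICC, class size, class count or number of cohorts is given. The largest figures, 12.1% and 21%, need only two classes and an ICC of 0.10. At 0.02 the effect is minor.

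**A shared instructor is not evidence of clustering.** The article never says how many instructors there are. One instructor for every class would add no variance between classes, and a common manual with fidelity monitoring would reduce it. The argument for clustering rests on interaction between class members.

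**The article is a condensed protocol and efficacy is secondary.** Both are true. However, the article does not leave the model or the sample-size method to another document. It states both, and neither matches the delivery it describes. Efficacy also sets the sample size.

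**With two to four classes, a random class effect is hard to estimate.** This stands. It argues for a sensitivity analysis rather than a new main model.

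**Conclusion.** The point holds in two parts, both limited to the secondary efficacy objective.

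Omitting the randomisation cohort is a certain mismatch between design and model. Its cost is modest: about 2-4% in the SE for assumed cohort ICCs of 0.05-0.10 with four balanced cohorts, in the conservative direction.

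Omitting class is a conditional risk in the other direction. Across the assumed range in the table, the true type I error would lie between 5.6% and 12.1%, somewhat lower if a shared cohort effect is also present. The documents cannot place the trial within that range, and they do not exclude an ICC of zero. The power paragraph's independence assumption is unstated and, if the class ICC is positive, optimistic.

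**What to change.** 1. Add cohort as a factor in the group-by-time model for POMS Total Mood Disturbance and the other patient-reported outcomes. Let it interact with time (equivalently, enter cohort in a model for change), because otherwise it does not reach the error term of the treatment contrast.
2. Add a sensitivity analysis for class clustering in the MBCR arm only. This can be a partially nested mixed model with small-sample degrees of freedom or, if that is unstable, SEs recomputed over a stated ICC range. Cohort as a factor does not deal with class clustering and removes its partial offset, so items 1 and 2 belong together.
3. Report the number and size of classes and the estimated ICC.
4. State in the power paragraph that the figure assumes no within-class correlation.

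The cost is a few lines of wording and model code, and a few degrees of freedom for cohort. With few classes, the class variance will be imprecise and the intervals in the sensitivity analysis wider. Recruitment was still open with 57 enrolled and the final analysis not yet available, so the changes can still be specified in advance. They need no change to conduct.

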### Masking

The nature of the group assignment and intervention does not allow for masking of participants. Research tasks are assigned to separate members of the team in order to ensure that primary investigators remain blind to participant status, and all questionnaires are completed online, attenuating the influence of bias on the part of research assistants.

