**Method/design:**

The study includes cancer patients in Alberta, exhibiting moderate distress, who do not have access to F2F MBCR. Participants will be randomized to either online MBCR, or waiting for the next available group. An anticipated sample size of 64 participants will complete measures online pre and post treatment or waiting period. Feasibility will be tracked through monitoring numbers eligible and participating through each stage of the protocol.

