The virtual classroom allows for multiple webcams to be viewed by all participants and instructor simultaneously. Online classroom access requires a password and the instructor ensures only approved participants are present in the class. Recorded versions of the classes are available through software that prevents download of the recording (provided through streaming video) as well as password access. This classroom feature allows the PI to monitor MBCR treatment fidelity throughout the trial. Class content and schedule follow the adapted F2F MBCR manual utilized by both PI and Co-I (Drs. [name] and [name] respectively) and course program published elsewhere [37]. Participants are able to access the manual online or receive a hard copy from research coordinators through post if preferred. The guided meditation recordings and videos are available for participants to download electronically. Participants are provided both orientation/instructions for set up of the new equipment and also an orientation session before the first class where headsets, webcameras, website and classroom functionality are tested and reviewed. This orientation session is completed before the start of the first MBCR class. Each participant is emailed a summary of dates and orientation material before the start of session one. Technical support is continuously provided by eMindful during all online sessions to address any technical issues with the hardware and software, while study related questions are directed to the research coordinators.

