### Meditation Log and attendance

Information on minutes spent in home practice of meditation and yoga is collected from each participant each week and returned to the study coordinator, which is shared with the group instructor. As part of the online virtual classroom capabilities, a basic feature of conference archiving is utilized. This feature can track all the MBCR classes with a list of attendees, and what time the participants entered and exited the classroom for attendance tracking.

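### The masking statement says the primary investigators stay blind, but the PI is given the class recordings for fidelity checks during the trial, so that blinding is not secured

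*Protocol article*

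**What the plan says.** The Masking section of the protocol article accepts that participants cannot be masked and offers two safeguards. One is online completion of all questionnaires. The other is a division of labour, with tasks given to different team members "in order to ensure that primary investigators remain blind to participant status".

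The section on the online MBCR intervention describes the classroom and its recordings. On the live class: "The virtual classroom allows for multiple webcams to be viewed by all participants and instructor simultaneously". On the recordings: "Recorded versions of the classes are available through software that prevents download of the recording", with password access. It then assigns a use and a user: "This classroom feature allows the PI to monitor MBCR treatment fidelity throughout the trial".

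The section on the meditation log and attendance adds, of the conference archive: "This feature can track all the MBCR classes with a list of attendees", together with each person's entry and exit times.

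On the control arm, the wait-list section says that, "following the wait period, the control group completes the online MBCR intervention".

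**The concern.** The masking statement makes investigator blinding depend on keeping tasks apart, yet the intervention section gives the PI a task that exposes who is in class. Both statements are in the current text, and nothing else in the article reconciles them.

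What is at stake is mainly the accuracy of a stated safeguard. In a trial with unmasked participants and self-reported efficacy outcomes, readers and risk-of-bias assessors will look at what the investigators knew. If the statement passes unchanged into the results report, the trial will be credited with a property its procedures do not secure. Beyond that, a PI who knows allocation could be influenced in conduct, data handling or interpretation, although the article gives no basis for sizing this.

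**Working it through.** No figure is involved, so the check is whether the masking statement can hold alongside the procedures.

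1. **What is promised.** Masking: task separation is meant to guarantee that the primary investigators do not know participants' allocation.

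2. **Who reviews fidelity, and when.** Intervention section: the PI is named as the monitor, and the monitoring runs over the course of the trial. This cannot be read as a review that begins only after the analysis is finished.

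3. **What the reviewer would see.** The intervention section describes streamed video and audio of both instructor and group members, with several webcams on screen at once. The attendance section says the archive carries an attendee list. No section says that recordings are de-identified, that participants' images or names are hidden, or that someone other than the PI does the review. It is therefore likely that participants can be identified, but this is inferred from the description of the classroom and archive.

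4. **Whether attendance reveals the arm.** Allocation takes place once a cohort has been assembled (Screening, consent and enrollment). Between a participant's own T1 and T2, only those allocated to immediate MBCR attend; controls come to class after the wait. Two cases follow:
   - *First cohort.* No former wait-list participant can yet be in the class, so attendance means immediate MBCR.
   - *Later cohorts.* The abstract says: "Participants will be randomized to either online MBCR, or waiting for the next available group". A later class may therefore mix newly allocated participants with earlier controls. Attendance then reveals the arm only to someone who also knows the person's cohort.

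5. **Result.** If the PI carries out the monitoring described, identifies participants and knows cohort timing, the PI can infer immediate-arm allocation during the trial. The blinding promised in step 1 is then not secured.

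6. **Which routes to bias remain.** Screening, the distress screen and consent precede randomization, so knowledge of allocation cannot distort by arm who is classed as eligible or as declining. The completion measure under the feasibility objective is a single proportion, completed over consented, with no comparison between arms. The normality check depends on outcome scores, which a class recording does not show. What remains is a general influence on post-randomization conduct, data handling, analysis and interpretation.

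**The case against.** The strongest reply is that this is a tension in wording with little effect on the results. The fidelity sentence says the feature permits monitoring; it does not say how many recordings the PI watches. The webcam sentence describes the live class as participants and instructor see it, not the recorded image. Fidelity review concerns delivery against the manual and so centres on the instructor. No outcome is rated by an investigator, questionnaires are completed online, allocation is computer-based and unpredictable, and analysis comes after the study ends. A condensed article may also leave the operating detail of fidelity review to a fuller document.

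Much of this stands. It limits the probable bias and makes identifiability an inference. It does not remove the conflict. The article makes a positive claim of assured blinding and, elsewhere, names the PI as the person for whom the recordings serve as a fidelity monitor. If the PI does not in fact view them, the text should say who does.

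Two stronger readings are tempting, and the article supports neither. A reader might infer that the allocation of the whole immediate arm is exposed and that wait-list status follows from absence. That would require the PI to watch recordings from every cohort, recognise every participant, know cohort timing and hold the full list of randomized people; none of this is stated. A reader might also infer that investigator blinding was the trial's chief protection against bias. It is one of two safeguards in the Masking section, alongside online questionnaires.

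**Conclusion.** The point holds in a limited form: the claim that the primary investigators remain blind is not supported by the procedures described. The conclusion assumes that the PI uses the recordings during the trial as the text allows, that participants can be identified from video, audio or the attendee list, and that the PI knows cohort timing. The last assumption is not needed for the first cohort if its classes can be recognised as such. The sentence on fidelity names the PI only, so the text shows the conflict for that role and is silent on whether other investigators view recordings.

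The size of any bias cannot be calculated from the article and is likely to be small, for the reasons conceded above. This is a correction to a stated safeguard. It is not evidence that the treatment comparison is distorted.

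**What to change.** Adopt one of two changes and make the Masking and intervention sections agree:

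- **Correct the claim.** Restrict the masking statement to the roles that are actually blind, name them, and report the primary investigators as unblinded. This costs only wording.
- **Correct the task.** Have fidelity review during the trial done by an existing team member who holds no blinded role, and keep the recordings and attendee lists from the PI until the analysis is final. The price is that the PI loses direct fidelity oversight while the trial runs. The article does not identify a suitable reviewer, and the class instructor should not assess their own delivery, so the sponsor must confirm that such a person exists before choosing this option.

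As an optional addition under either choice, run the T1-T2 outcome analysis on coded arm labels, with model decisions fixed before the code is opened. Only controls complete T3, so T3 data must be withheld until then or the coding is broken at once. This costs little and was still possible when the article was written: recruitment was continuing and the comparative analysis was not yet available.
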